## **9. Statistics**

Because there is no data available on high-sensitivity troponin T release after pacemaker implantation, historic data from patients supplied with pacemakers in the German Heart Centre 2011 were used for sample size calculation. For this, data of the most recent 30 patients (most recent 15 patients with active fixation ventricular leads and most recent 15 patients with passive fixation ventricular leads) with available high-sensitivity troponin T levels before and after pacemaker implantation were analysed. They did not differ relevantly in their baseline

characteristics and the distribution of high-sensitivity troponin T plasma concentrations is shown in the following table.

[figure not shown]

A=active fixation; P=passive fixation;

delta.hsTroponin refers to change plasma concentrations measured in ng/ml

The distribution is non-normal and due to large variations in the values including negative increases of plasma concentration after pacemaker implantation a non-parametric test (Mann-Whitney U Test) is the most appropriate approach to sample size estimation.

Null hypothesis: The probability that a randomly selected patient of the study cohort who received an active fixation ventricular pacemaker electrode shows a larger increase of high-sensitivity troponin T after implantation than a randomly selected patient who received a passive fixation ventricular pacemaker lead is 50 %.  $H_0: P(A > P) = P(P > A) = 50\%$ .

In the cohort of historic patients from the German Heart Centre the above mentioned probability was  $P(A > P) = 59\%$ . For sample size calculation it was assumed that an effect of  $P(A > P) = 60\%$  or  $P(P > A) = 60\%$  would determine the least difference that would be considered as clinically relevant..

Assuming that there is a relevant difference between both groups, a total of 262 patients need to be recruited (131 patients per group) to find a significant effect with a probability (=power) of at least 80% on a two-sided level of significance of  $\alpha=5\%$  (10).

Assuming a drop-out rate of 10% for this acute study, a total of 290 patients (145 patients per group) will be enrolled in the study.

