### **5. Study procedure:**

After obtaining written informed consent to the pacemaker implantation and the study participation the baseline high-sensitivity troponin T plasma concentration will be determined. This will be done from a previously taken blood sample provided for standard clinical tests if the sample is not older than 24 hours. If no such sample is available or if retrospective analysis is not possible an additional blood sample is required. Prior to pacemaker implantation the patient will be randomly assigned to receive a CE-marketed, commercially available, ventricular passive or active fixation electrode. Randomisation will be stratified for single- and dual-chamber pacing and for centres in a 1:1 ratio between active fixation and passive fixation leads for right ventricular pacing; for atrial leads active fixation will be used. The randomisation will be performed in varying blocks for each of stratify and will be centrally generated in the Deutsche Herzzentrum München. The participating centres will be provided with sealed envelopes containing the randomisation information. During pacemaker

implantation all necessary – and clinically reasonable - efforts should be made to adhere to the randomised lead type. Cross-overs (to avoid unsuccessful pacemaker implantations) will be allowed on the basis of the individual judgement of the implanter. In case of cross-over, the primary endpoint will be evaluated on an intention-to-treat basis. After pacemaker implantation, the patient will be followed according to standard clinical practice. Standard clinical practice includes the drawing of blood samples post-implantation (usually the next morning). For study reasons this should be done between 6 and 24 hours after pacemaker implantation. On this occasion, additionally to the routine parameters, high-sensitivity troponin T plasma concentration will be determined. The patients will be followed for three months with respect to lead performance, necessity of lead revision and mortality.

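### Randomisation is stratified by chamber type and centre, but the null hypothesis, sample size and AUC rule are framed for a pooled comparison; if the strata predict troponin change, this is conservative and gives away some efficiency

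*Protocol*

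**What the plan says.** On allocation, protocol section 5 (Study procedure) states: "Randomisation will be stratified for single- and dual-chamber pacing and for centres in a 1:1 ratio". It uses varying blocks within strata and adds that "for atrial leads active fixation will be used". Each dual-chamber patient, in either arm, therefore has a second, actively fixed lead.

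On inference, section 9 (Statistics) states that "a non-parametric test (Mann-Whitney U Test) is the most appropriate approach to sample size estimation". Its null hypothesis concerns the whole cohort: "The probability that a randomly selected patient of the study cohort who received an active fixation ventricular pacemaker electrode shows a larger increase" than a passive-fixation patient is set at 50%. The least relevant effect is 60% in either direction. The resulting size is stated as "a total of 262 patients need to be recruited (131 patients per group"); the planned power is 80% at a two-sided 5% level. The non-inferiority paragraph of the same section compares the lower 95% limit of a two-group AUC with 0.45.

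Chamber and centre appear in none of these elements. Baseline hs-troponin T enters only by subtraction, since section 6 (Endpoints) defines the primary endpoint as post-implantation minus pre-implantation concentration. Only the protocol is at hand; a statistical analysis plan may exist.

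**The concern.** Blocking within strata removes between-stratum differences from the comparison of the arms. A pooled test or interval still counts those differences as random variation, so its standard error is too large whenever the strata are prognostic. The test then rejects too rarely under the null, the interval over-covers, and a test that uses the strata would have more power.

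The protocol gives reason to expect some prognostic effect. Section 1 attributes troponin release to direct trauma from the leads, section 5 gives dual-chamber patients a second fixation site, and section 6 lists single or dual chamber among the factors to be related to post-implantation troponin.

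The AUC step is where this could matter most. Section 2 expects no relation between lead type and troponin rise, so the trial's conclusion may well rest on that interval.

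**Working it through.** **Inputs from section 9:** two-sided 5%, power 80%, P = 0.60, 131 per group. **Assumption:** the strata explain a share R of the variance of troponin change (normal scale). The protocol gives no value, so R is varied from 0 to 30%.

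**1. The plan's own figure (Noether).** N = (1.960 + 0.842)² / (12 × 0.5 × 0.5 × 0.10²) = 261.6, rounded up to 262. The stated figure reproduces. At N = 262 the drift is √(3 × 262) × 0.10 = 2.804, and power = Φ(2.804 − 1.960) = 80.1%.

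**2. Pooled test after blocked randomisation.** The true variance of the pooled statistic is about (1 − R) times the variance the test uses.
- Size = 2Φ(−1.960/√(1 − R)).
- Power at cohort-wide P = 0.60: Φ((2.804 − 1.960)/√(1 − R)).

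**3. Stratified test, same treatment effect.** The within-stratum probability is Pw = Φ(0.2533/√(1 − R)), where 0.2533 = Φ⁻¹(0.60). Power ≈ Φ(√786 × (Pw − 0.5) − 1.960).

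Simulation check: 262 patients, normal outcomes with cohort-wide P = 0.60. The first run used 10 unequal strata, blocks of 4 and 6, and 4,000 null and 2,000 alternative trials per setting. Monte Carlo error was about 0.35 points for size and 0.9 for power. Ranges are over two runs; the 5% row has one.

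| R | Pooled size %, formula / simulated | Pooled power %, formula / simulated | Pw | Van Elteren power %, formula / simulated |
|---|---|---|---|---|
| 0 | 5.0 / 4.7–5.1 | 80.1 / 80–81 | 0.600 | 80.1 / 79–80 |
| 5% | 4.4 / 4.9 | 80.7 / 80 | 0.603 | 82.0 / 80 |
| 10% | 3.9 / 3.5–4.0 | 81.3 / 81–82 | 0.605 | 83.9 / 83–84 |
| 20% | 2.8 / 2.6–2.9 | 82.7 / 83 | 0.612 | 87.8 / 86–87 |
| 30% | 1.9 / 2.1–2.6 | 84.3 / 83–84 | 0.619 | 91.6 / 90–92 |

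The van Elteren size stayed at about 5% (4.9 to 5.6%).

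**4. AUC interval when the true AUC is 0.50.** The usual standard error is √(263/(12 × 131 × 131)) = 0.0357, so the half-width is 0.070 and the observed AUC must exceed 0.52 for the lower limit to clear 0.45. At R = 20% the true standard error of the pooled AUC is 0.0357 × √0.8 = 0.0320.
- Interval as usually computed: chance of clearing 0.45 = 1 − Φ(0.0200/0.0320) = 27%.
- Same AUC with a variance that respects the strata: half-width 1.960 × 0.0320 = 0.063, chance 1 − Φ(0.0126/0.0320) = 35%.
- For R = 0, 10 and 30% the two chances are 29 and 29%, 28 and 31%, and 25 and 39%.

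A within-stratum AUC is a different quantity. Its standard error stays near 0.0357, so if 0.45 is applied to it unchanged the chance is 1 − Φ(0.0200/0.0357) = 29%. A cohort-wide 0.45 corresponds, at R = 20%, to Φ(−0.1257/√0.8) = 0.444 within strata. On that scale the chance is again 1 − Φ((0.0700 − 0.0559)/0.0357) = 35%. The gain at this step therefore depends on which scale the 0.45 refers to.

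**5. Baseline.** If baseline explains 10 or 20% of the change score, the simulated size of the pooled test is 4.9 or 5.1%, so it is not lowered. Power is 82 or 83% pooled, against 85 or 89% for rank ANCOVA with baseline.

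**The case against.** The strongest reply is that the quoted sentence concerns sample size estimation, section 6 names no test, and nothing in the protocol says the analysis must be unstratified. Stratification terms and pooling of centres commonly belong to the statistical analysis plan. This stands: a reader might infer that the protocol orders an unstratified primary test, and it does not. What remains is that the null, the sample size and the AUC rule are all worded for pooled groups, so a plan written to match them would naturally be pooled.

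A reader might also infer that the trial is underpowered. That follows only if 60% is fixed within strata. At R = 20% the cohort-wide probability is then Φ(0.2533 × √0.8) = 0.590, and pooled power is Φ((√786 × 0.0896 − 1.960)/√0.8), about 73%. The protocol's 60% is defined for patients drawn from the whole cohort, and on that definition the planned 80% is met.

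Two further inferences fail. That the error rate is below 5% cannot be asserted as fact, because no chamber or centre effect is given; in any case a conservative test does not inflate false positives. Omitting baseline does not lower the error rate either, since baseline is not a stratification factor and is already in the change score.

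The reply is also right that stratifying has a price. The estimand becomes a within-stratum probability, and with many very small strata the gain can shrink or reverse. The number of centres is not stated in the text at hand.

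**Conclusion.** The point holds as a conditional efficiency recommendation. It does not correct an error: 262 and the 80% power stand.

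If chamber and centre together explain 10 to 30% of the variance in troponin change, the pooled test runs at about 4% down to roughly 2 to 2.5% instead of 5%. Its power is about 1 to 3 points (at 10%) to 7 to 8 points (at 30%) below a van Elteren test. The usual interval for the pooled AUC is then 1/√(1 − R) times too wide, which is 5% at R = 10% and 20% at R = 30%. At R = 0 nothing material changes.

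These figures rest on the assumed R, normal outcomes with a common shift, and strata large enough to rank within. The direction is well supported; the size is unknown from the documents.

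**What to change.** - Name the primary test as a van Elteren test stratified by chamber type and centre, with a rule for pooling small centres fixed before the data are seen.
- Take the AUC and its 95% interval for the 0.45 criterion from a matching stratified estimator. State whether 0.45 refers to the within-stratum or the cohort-wide probability, because a narrower interval on the 0.45 scale arises only for a cohort-wide AUC with a stratum-based variance.
- Reword the null hypothesis as a within-stratum probability to match the test.
- Report the pooled Mann-Whitney test and AUC as sensitivity.
- Optionally add baseline hs-troponin T through rank ANCOVA, as an efficiency gain only.

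The cost is protocol or analysis-plan wording and a few lines of code, with no new data or patients. The downside is a slight loss of power if strata are very small or not prognostic, and a within-stratum in place of a cohort-wide estimand.

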#### Assessment of non-inferiority:

If the study fails to find statistical evidence for superiority of one method compared to the other, non-inferiority will be concluded, if the lower limit of the 95% confidence interval for the area under the ROC curve (AUC) is greater than 0.45. The AUC estimates the probability that the change in high-sensitivity troponin T plasma concentration is greater in a randomly selected patient treated with one method compared to a random sample from patients treated with the other method.

#### **10. Study start:**

Planned after ethics committee approval 03/2012

